#### Brief Intervention

For control arm participants, usual care will be provided. Screening scores will be manually computed and entered into the EMR by a clinician trained in SBIRT. Clinician will deliver brief intervention to participants who score moderate to high risk in any substance without technology-enhanced intervention.

For intervention arm participants, the brief intervention in the primary care office will consist of 4 steps.

Participant will be asked to rate his or her willingness to quit for all his or her at-risk substances on the iPad app.

For the substance he or she is most likely to quit, the participant completes a brief 2-part intervention using an iPad app: watching a 3-minute educational video about the substance and its risks and completing an exercise to name the pros and cons of quitting this substance (Figure 3).

When the clinician comes into the room, the participant hands the iPad over to the clinician. The clinician now has an overview of screening results, readiness to change for at-risk substances, and the participant’s personal pros and cons for the change. The clinician will conduct the brief intervention in person (Figure 4).

At the end of the brief intervention, the clinician will ask the participant to rate readiness for change again. They will work together to set up quitting or reducing use goals for at least one at-risk substance. At the end, the participant will sign on the screen and commit to the goals (Figure 5).

**Figure 2 figure2:**
[figure not shown]
Dynamic branching screening tool, participant view.

**Figure 3 figure3:**
[figure not shown]
Brief intervention, participant view.

**Figure 4 figure4:**
[figure not shown]
Brief intervention, clinician view.

**Figure 5 figure5:**
[figure not shown]
Setting goals, participant view.

#### Referral to Treatment

If the participant is screened at high risk for any substance and the clinician and participant mutually agreed to specialty follow-up treatment, the clinician can easily refer the participant to a specialty treatment program affiliated with this study from the iPad app. The participant referral data is also integrated into EMR.

#### Follow-Up

The control arm participants will receive no additional follow-up beyond usual care until the 30 days’ end.

The intervention arm participants will receive a once-per-day reminder to answer daily follow-up questions. The questionnaire screen includes:

Reminder for specialty care appointment the day before the appointment. The user can reschedule the appointment from the questionnaire screen. The questionnaire also asks whether the user went to the appointment on the day after.Adherence by participant to each of his or her own stated goals on that day.Using items from a drug use self-monitoring log developed by Sobell and Sobell [16], participants will be asked to report details of their drug and alcohol use within the last 24 hours, including drugs used, drinks had, cravings or urges to use drugs or drink alcohol, situations related to drug use (eg, patient was alone, in a social situation), and thoughts or feelings experienced when using drugs or during urges.

In the event of strong craving or substance use, the user is instructed to access an EMA screen bookmarked on his or her phone. The event-based EMA measures craving and surroundings at the time of craving or substance use.

Adapted from the 3-item Opioid Craving Scale by McHugh et al [31], participants will be asked to rate on a scale from 1 to 10 how much they currently crave a drug, how strong their desire to use has been when something in the environment reminded them of the drug, and the likelihood that they would use the drug in a specific environment.EMA items on psychological mood are adapted from an EMA assessment conducted by Gwaltney et al [32] and are designed to assess the participant’s affect state associated with substance use. The items ask participants to rate to what extent they feel happy, stressed, relaxed, bored, irritable, energized, and sleepy.

A risk score will be computed for every intervention participant every day. The score depends on the participant’s questionnaire adherence, self reported goal adherence, and substance use. If a participant is at high risk, he or she may be offered the brief intervention video to watch again.

The risk score and individual participant summaries will be made available to the participant’s clinicians, including a primary care physician and the study coordinator who also serves as a substance use coach, via a Web-based dashboard (Figure 6). If the clinicians determine that the participant’s follow-up pattern or answers indicate high-risk substance use behavior, they may make additional referrals for the participant.

**Figure 6 figure6:**
[figure not shown]
Web-based dashboard for intervention or additional referral, clinician view.

#### Surveys

At the end of the primary care clinic visit, all participants will be asked to complete a survey about their experience with the process and their knowledge about SUDs. The intervention group patients will also be asked about their acceptance of the technology solution. The survey has the following components:

A 19-item validated computer system usability questionnaire is used to evaluate a computer system’s usability [33]. It also allows users to give free form answers on what he or she likes or dislikes about the system. We use it to evaluate the iPad tool in primary care clinics.A questionnaire based on the unified theory of acceptance and use of technology (UTAUT) by Venkatesh et al [34] is used to evaluate the technology solution’s ease-of-use, perceived usefulness, and the user’s social and facilitating conditions to predict the adoption of such technology solutions. The original UTAUT questions will be adapted to reflect our product.A 10-item validated patient satisfaction questionnaire will evaluate patient satisfaction with primary care providers [35].The ASI–Lite asks for drug use in the previous month, comorbid medical and mental illness, and social and legal outcomes related to drug use [36]. The ASI score is a quantitative measure of the user’s substance use.

At the end of the 30-day follow-up period, all participants will be asked to complete the screening, patient satisfaction, and ASI questionnaires again. They will also be asked to report any health care service they received during the 30 days, including any specialty SUD services. They can complete those questions on a computer or on paper. A complete schedule of all participant surveys and questionnaires is listed in Table 1.

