### Hypotheses

The RCT will address 2 primary hypotheses. Hypothesis 1 has 7 secondary hypotheses. Compared with the control group,

Significantly more intervention group patients will receive specialty SUD care within 30 days following the SBIRT encounter at the primary care clinic. The secondary hypotheses attempt to explain how and where the increased specialty care utilization occurs in the process.More intervention group patients are diagnosed with high-risk SUD.More intervention group patients are subsequently referred to specialty care at the end of the primary care clinic encounter.More intervention group patients are referred to specialty care during the 30-day following period due to failing to adhere to goals.Intervention group patients are more satisfied with the care they receive.Intervention group patients are more knowledgeable about SUD.Intervention group clinicians are more satisfied with the process.Intervention group clinicians spend less time on the SBIRT intervention and follow-up.Intervention group patients will report a greater reduction in substance use and a greater drop in Drug Abuse Screening Test (DAST-10) and Addiction Severity Index (ASI) scores within 30 days.

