### Trial Process

#### Timing and Flow of the Randomized Controlled Trial

We will conduct an RCT with 500 patients with SUD risk in the UHD Clinic, a large academic primary care provider affiliated with a major public university. Recruited patients will be randomized into control and intervention arms. Both arms will take initial baseline and exit (30 days) surveys to evaluate self-reported substance use and specialty service utilization. The control arm patients will receive usual care. The intervention group patients will receive technology-enhanced SBIRT with a mobile follow-up program to track goals and substance use at home. The RCT will be managed by a team of seasoned SBIRT and addiction researchers and practitioners at the research site.

The RCT tracks participants for 30 days after the primary care encounter. We will collect feedback from the patients during the 30 days and count the number of patients who use specialty care services in specialty care programs for tobacco, alcohol, and drug abuse (both from self-reporting and from the service providers).

Since the clinical trial involves more than 9 human subjects, the RCT will be approved by the OMB as well as the university’s Institutional Review Board (IRB), which is responsible for research in the university affiliated health care providers. Figure 1 displays the flow of participants.

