#### Clinician Interviews

At the end of the study, all participating clinicians will be interviewed and debriefed on a one-to-one basis. Some clinicians will have worked on both arms of participants and can provide valuable insights on where the technology solution succeeded and where it still needs improvements. Clinician acceptance is a critical factor for successful commercialization and dissemination of the technology intervention in the future.

**Table 1 table1:** Schedule of survey and questionnaire completion by study arm.

	Intervention arm				Control arm		
	Screening	End of PCP^a^ visit	Follow-up	30 days	Screening	End of PCP visit	30 days
One question screener	x				x		
My Own Health Record	x				x		
PHQ-9^b^	x				x		
AUDIT-C^c^	Optional			x	x		x
DAST-10^d^	Optional			x	x		x
Change readiness		x		x	x		x
Technology acceptance (UTAUT^e^)		x					
Computer system usability		x					
Patient satisfaction		x		x		x	x
Addiction Severity Index–Lite		x		x		x	x
Goal adherence			Daily				
Psychological mood			EMA^f^				
Context/surroundings			EMA				
Substance use			Daily				
Substance craving scale			EMA				
Referral adherence			Optional				
Specialty care utilization				x			x

^a^PCP: primary care provider.

^b^PHQ-9: Patient Health Questionnaire.

^c^AUDIT-C: Alcohol Use Disorders Identification Test.

^d^DAST-10: Drug Abuse Screening Test.

^e^UTAUT: unified theory of acceptance and use of technology.

^f^EMA: ecological momentary assessment.

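### The only starting ASI-Lite for the drop predicted in primary hypothesis 2 is collected after randomisation and the brief intervention, so a differential reporting shift could bias an ASI change comparison

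*Protocol article*

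**What the plan says.** All references are to the protocol article.

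- **Outcome.** Under Hypotheses, primary hypothesis 2 predicts for the intervention arm "a greater drop in Drug Abuse Screening Test (DAST-10) and Addiction Severity Index (ASI) scores within 30 days".
- **First ASI.** The Surveys section states "At the end of the primary care clinic visit, all participants will be asked to complete a survey" and lists the ASI-Lite among its components. At the end of follow-up, "all participants will be asked to complete the screening, patient satisfaction, and ASI questionnaires again".
- **Schedule.** In Table 1 the row "Addiction Severity Index–Lite" is marked in the End of PCP visit and 30 days columns in both arms, and under Screening in neither. DAST-10, the companion measure, does appear under Screening (as optional in the intervention arm).
- **Order of events.** The sections run consent, randomisation, screening, brief intervention. Under Brief Intervention, "For intervention arm participants, the brief intervention in the primary care office will consist of 4 steps". These include a video, a pros-and-cons exercise and a session with the clinician, and they close with "At the end, the participant will sign on the screen and commit to the goals".
- **Control visit.** The same section gives controls usual care, including a clinician-delivered brief intervention, without the technology, for those at moderate to high risk in any substance.
- **General statement.** Timing and Flow says "Both arms will take initial baseline and exit (30 days) surveys to evaluate self-reported substance use and specialty service utilization".

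**The concern.** A drop needs a starting value. For DAST-10 that value precedes the brief intervention. For the ASI it does not: the first form is filled in after the arms have been treated differently.

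Someone who has just watched a video about a substance's risks and signed a goal may disclose more than they otherwise would, or may give more socially acceptable answers. If this happens to a different degree in the two arms, the starting ASI differs between arms for a reason unrelated to past use. That difference passes in full into the between-arm contrast in drop. More disclosure in the intervention arm would look like benefit; less would hide benefit. A larger sample does not remove the bias. For the same reason, the end-of-visit value is not a sound baseline covariate.

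**Working it through.** **1. The plan's own figure.** For primary hypothesis 2 the Power Calculation section gives 86 per arm (two-sided 5%, power 0.9, medium Cohen effect, taken here as 0.5 SD).

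- Normal approximation: 2 × (1.960 + 1.282)² / 0.5² = 84.1, so 85.
- Two-sample t test: 85.03, so 86. The stated figure is reproduced.

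This calculation compares 30-day means and uses no baseline. No stated sample size depends on when the ASI-Lite is given.

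**2. What bias would a reporting shift cause?** Let drop = first ASI − 30-day ASI, in SD units. Let δ be the true between-arm difference in drop, and b the extra shift in the intervention arm's first report caused by the iPad session. The expected estimate is δ + b. The document gives no value for b, not even its sign.

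**3. Illustrative inputs.**

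- Analysed per arm: 500 / 2 × (1 − 0.20) = 200, from the total sample and attrition in the Power Calculation section.
- Pre-post correlation ρ: 0.3 to 0.7 (assumption).
- Shift |b|: 0.1 or 0.2 SD (assumption).
- δ = 0, equal SDs, two-sided 5% test, normal approximation.

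**4. Formulas.** The SD of a change score is √(2(1 − ρ)), so SE = √(2(1 − ρ)) × √(2/200) = √(4(1 − ρ)/200). The rejection rate is Φ(|b|/SE − 1.96) + Φ(−|b|/SE − 1.96).

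| ρ | SE | Rejection, \|b\| = 0.1 | Rejection, \|b\| = 0.2 |
|---|---|---|---|
| 0.3 | √0.014 = 0.118 | 0.135 | 0.394 |
| 0.5 | √0.010 = 0.100 | 0.170 | 0.516 |
| 0.7 | √0.006 = 0.077 | 0.252 | 0.733 |

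With b = 0 the rate is 0.05. So an assumed 0.1 SD shift gives about 14-25%, and 0.2 SD about 39-73%. The range widens with ρ because a higher correlation makes the change score more precise while the bias stays the same.

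**5. Which analyses would be exposed?**

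- The drop in ASI as worded in primary hypothesis 2: exposed.
- The drop in DAST-10: not exposed to this problem, since its first value is taken at Screening.
- A comparison of 30-day ASI means, the form used in the Power Calculation section: not exposed, since the first ASI does not enter.

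**The case against.** The case for leaving this alone has several parts.

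- **The ASI-Lite asks about the previous month.** The visit cannot change what happened then. This stands: the mechanism is reporting only, and nothing in the document shows that such a shift occurs.
- **Controls are also measured after a visit, often with counselling.** This stands too. Only the increment from the technology-enhanced steps can bias the contrast. That increment is, however, part of the treatment under test, so it cannot be assumed to be zero.
- **The analysis section does not name the ASI.** Hypotheses Testing applies difference in differences to amount and frequency of use and to DAST-10, and the Results section restates the hypothesis without the ASI. This narrows the point to one component of a primary hypothesis. It does not remove it, because the Hypotheses section names the ASI drop and the abstract repeats it. A reader might infer that the ASI-Lite also supplies the amount and frequency data, so that the regression is affected as well. That is possible, but the document does not say which instrument supplies them.
- **There is a baseline.** A reader might infer that the promised initial survey is missing altogether. It is not: one-question screeners, AUDIT-C and DAST-10 are scheduled at Screening and plausibly meet that promise. Only the ASI lacks a pre-intervention value.
- **Power is planned on 30-day means.** This is correct, and such a comparison avoids the problem. It also means that one cannot say a 0.2 SD shift takes 0.2 from the planned 0.5 SD: the planned effect refers to 30-day means, where the starting ASI plays no part.

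**Conclusion.** The point holds for the ASI component of primary hypothesis 2. The text and Table 1 agree that the first ASI-Lite is completed at the end of the visit in both arms, after randomisation and the brief intervention. A drop in ASI computed as worded therefore starts from a post-treatment value and is open to a differential reporting shift.

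The timing is certain; the size and direction of any bias are not. The false-positive rates of about 14-25% and 39-73% rest wholly on assumed shifts of 0.1 and 0.2 SD, with 200 per arm, correlation 0.3 to 0.7 and no true effect. They show how sensitive a change-score test would be. They do not estimate what will happen in this trial.

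The document does not support concluding that the trial has no baseline, that primary hypothesis 2 as a whole is compromised, or that the sample size is wrong.

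**What to change.** **Participants not yet enrolled.** Give the ASI-Lite after consent and before randomisation in both arms. Keep the satisfaction, knowledge, usability and UTAUT items at the end of the visit. Amend Table 1 and the Surveys section to match.

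**Participants already enrolled, and the main ASI comparison if timing is mixed.** Compare 30-day ASI between arms without using the end-of-visit value as a baseline or covariate. Adjust instead for the pre-intervention DAST-10 where available. Report the unadjusted comparison alongside, because DAST-10 is also collected after allocation, and on paper in one arm and iPad in the other. State this rule before the data are analysed, and reword the ASI part of primary hypothesis 2 to match.

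**Cost.** No new instrument and no change in sample size. Patients wait somewhat longer before the visit. The Results section says data collection is well underway, so a pre-visit ASI cannot be recovered for those already enrolled, and the new order would apply only to the remainder. The change would also have to go through the OMB and IRB approvals that the protocol describes. If enrolment has finished, only the analysis rule applies, and it costs nothing beyond writing it down.

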#### Clinician Interviews

At the end of the study, all participating clinicians will be interviewed and debriefed on a one-to-one basis. Some clinicians will have worked on both arms of participants and can provide valuable insights on where the technology solution succeeded and where it still needs improvements. Clinician acceptance is a critical factor for successful commercialization and dissemination of the technology intervention in the future.

**Table 1 table1:** Schedule of survey and questionnaire completion by study arm.

	Intervention arm				Control arm		
	Screening	End of PCP^a^ visit	Follow-up	30 days	Screening	End of PCP visit	30 days
One question screener	x				x		
My Own Health Record	x				x		
PHQ-9^b^	x				x		
AUDIT-C^c^	Optional			x	x		x
DAST-10^d^	Optional			x	x		x
Change readiness		x		x	x		x
Technology acceptance (UTAUT^e^)		x					
Computer system usability		x					
Patient satisfaction		x		x		x	x
Addiction Severity Index–Lite		x		x		x	x
Goal adherence			Daily				
Psychological mood			EMA^f^				
Context/surroundings			EMA				
Substance use			Daily				
Substance craving scale			EMA				
Referral adherence			Optional				
Specialty care utilization				x			x

^a^PCP: primary care provider.

^b^PHQ-9: Patient Health Questionnaire.

^c^AUDIT-C: Alcohol Use Disorders Identification Test.

^d^DAST-10: Drug Abuse Screening Test.

^e^UTAUT: unified theory of acceptance and use of technology.

^f^EMA: ecological momentary assessment.

### Data Collection and Analysis

#### Data Sources

In this RCT, we collect data from 2 primary sources: the participant self-reported data through surveys and questionnaires and clinic-reported utilization from reports.

#### Surveys and Questionnaires

Each participant will complete multiple surveys and questionnaires at various points during this study (see Table 1).

#### Hypotheses Testing

Since the hypotheses are primarily concerned about the observed differences between control and intervention arms, including referral rates, satisfaction level, knowledge level, and greater reduction in substance use, Student *t* tests will be used.

A chi-square test will be performed on the proportions of participants who receive specialty care to detect the significance in the difference between control and intervention arms. This test will be repeated for participants who have self-reported receiving specialty care. A chi-square test will be performed on the proportions of participants who receive specialty care referral at the end of the primary care encounter and who receive a specialty care referral during the 30-day follow-up period. For each question in the participant satisfaction survey and on the overall computed satisfaction and knowledge score, we will perform a *t* test for the answer’s mean value. Clinician interview results will be evaluated qualitatively to determine clinicians’ satisfaction with the solution.

Difference in differences regression tests will be performed on the differences in self-reported substance use amount and frequency and DAST-10 scores measured at baseline and 30 days of the study. The correlation coefficients and their confidence levels will be computed. These tests detect difference in drug use changes from control and intervention groups during the intervention period.

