#### Randomization

The study coordinator will then use an online random number generator (randomizer.org) to randomize the participant to either the control or intervention group.

The study administrator will then search for the patient name in the SBIRT application’s admin console. The admin console searches the connected electronic medical record (EMR) records and retrieves the patient data to populate the study’s database. The patient participant’s arm will be noted in the database record.

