#### Power Calculation

For primary hypothesis 1, we will perform a chi-square test to evaluate the difference in proportions of participants who receive specialty care in the 2 arms. We estimate that SBIRT intervention [37] could result in 10% to 30% of patients receiving specialty care. We computed power using the following assumptions: chi-square for 2 proportions, 2 samples, and 2-sided test; type 1 error rate of 5%; power of 0.9; control arm with 20% participants receiving specialty care; intervention arm with 35% participants receiving specialty care; and same number of participants in control and intervention. A sample of 197 participants in each of arms will be sufficiently powered to detect such differences between control and intervention arms.

For primary hypothesis 2, we assume that both arms start with the same levels of substance use. Therefore, to test the hypothesis, we will test the mean substance use levels at 30 days for both arms. We computed power for the sample *t* test of the mean using the following assumptions: 2-tailed *t* test for the mean of 2 samples; type 1 error rate of 5%; power of 0.9; medium Cohen effect size; and same number of participants in control and intervention. A sample of 86 participants in each arm will produce sufficient power. Based on the above calculation and considering up to 20% attrition, a sample of 500 total participants will have sufficient power to test both primary hypotheses.

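### The unadjusted chi-square for receipt of specialty care is valid, but it makes no use of pre-randomisation EMR information; a prespecified adjusted risk difference would be a modest, low-cost gain

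*Protocol article*

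**What the plan says.** Two sections of the protocol article fix the same test for primary hypothesis 1. Hypotheses Testing plans a chi-square test "on the proportions of participants who receive specialty care to detect the significance in the difference between control and intervention arms". Power Calculation states: "we will perform a chi-square test to evaluate the difference in proportions of participants who receive specialty care in the 2 arms", and sizes the trial on a "chi-square for 2 proportions, 2 samples, and 2-sided test". Neither names a covariate.

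Other sections bear on the point:

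- **Eligibility (textbox):** entry rests on one positive answer about illegal drug use, or nonmedical use of a prescription drug, in the past year.
- **Referral to Treatment:** the route to specialty care at the visit opens with "If the participant is screened at high risk for any substance" and also needs agreement between clinician and participant.
- **Randomization:** the arm is drawn with an online random number generator, and no stratification is mentioned. Then: "The admin console searches the connected electronic medical record (EMR) records and retrieves the patient data". The fields retrieved are not listed.
- **Screening:** the control arm completes the screeners on paper and the intervention arm on an iPad app, so screening follows the draw.
- **Hypotheses:** one secondary hypothesis is that more intervention patients will be diagnosed as high risk.
- **Surveys and Table 1:** the first ASI-Lite is completed at the end of the primary care visit.

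**The concern.** The entry criterion admits anyone from an occasional user to a person with a serious disorder, whereas referral at the visit is aimed at those screened as high risk. It is reasonable to expect that people who were more severe before the visit are more likely to receive specialty care in either arm. A raw comparison of two proportions leaves that variation in the error term. With an unstratified draw, any chance imbalance in severity also passes into the observed difference.

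The article plans a regression using baseline values for hypothesis 2 (difference in differences), but nothing comparable for hypothesis 1, which drives the sample size. Adjusting for values fixed before randomisation keeps the type I error and usually improves precision. At stake is some power on the main endpoint, chiefly if the true effect is smaller than the 15 points assumed.

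**Working it through.** **Inputs from Power Calculation:** "type 1 error rate of 5%; power of 0.9; control arm with 20% participants receiving specialty care"; intervention arm 35%; equal arms; 197 per arm; up to 20% attrition; 500 in total. Completers per arm at full attrition: 500 × 0.8 / 2 = 200.

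**Input not in the documents:** R², the share of outcome variance explained by pre-randomisation covariates. Assumed range 0.02 to 0.10.

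**Step 1. Reproduce the stated size.** With mean proportion (0.20 + 0.35)/2 = 0.275:

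n = [1.96 √(2 × 0.275 × 0.725) + 1.2816 √(0.20 × 0.80 + 0.35 × 0.65)]² / 0.15² = 184.1

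Continuity correction: (184.1/4) × [1 + √(1 + 4/(184.1 × 0.15))]² = 197.2. This agrees with the stated 197. Attrition: 394 / 0.8 = 492.5, so 500 is enough. The plan's arithmetic is sound.

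**Step 2. Power of the test as planned, 200 per arm, no continuity correction.** The unpooled standard error is √[(0.16 + 0.2275)/200] = 0.0440. Then 0.15/0.0440 = 3.41, and power = Φ(3.41 − 1.96) = 92.6%. Pooling the variance under the null gives 92.2%. Both exceed the 90% target.

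**Step 3. Power after adjustment.** Approximate the variance of the adjusted difference as (1 − R²) times the raw variance:

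Power = Φ( δ / √[(p₁q₁ + p₂q₂)(1 − R²)/n] − 1.96 ), n = 200

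| Assumed R² | 20% vs 35% | 20% vs 30% |
|---|---|---|
| 0 | 92.6% | 64.2% |
| 0.02 | 93.1% | 65.1% |
| 0.05 | 93.8% | 66.5% |
| 0.10 | 94.9% | 68.8% |

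The gain over R² = 0.02 to 0.10 is 0.5 to 2.3 points at the planned effect and 0.9 to 4.6 points at the smaller one. The 30% intervention rate is an illustration; it is the top of the 10% to 30% range that the article gives for patients reaching specialty care through SBIRT.

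**Step 4. Check the approximation.** Logistic regression with one continuous pre-randomisation covariate was simulated (200 per arm, 3,000 trials per setting, 20% vs 35%). With 3.8% of control-arm variance explained, the standardised difference had 0.96 times the raw variance, and power was 93.1% against 92.0% for the chi-square. With 13.4% explained, the ratio was 0.86 and power was 96.4% against 93.7%. The variance ratios match 1 − R².

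**Step 5. Which measures may be used.** Set the schedule beside the draw:

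- DAST-10 and AUDIT-C follow randomisation, are taken in a different mode in each arm, and feed a risk class that the trial expects to differ by arm.
- ASI-Lite follows the brief intervention.
- EMR retrieval also comes after the draw, but entries dated before the visit cannot have been changed by the arm.

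Of the severity information discussed here, only the last is safe to adjust for.

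**The case against.** The strongest case against the point is that nothing is stated wrongly. A chi-square is valid in a randomised trial, chance imbalance is already covered by the 5% error rate, the test matches the sizing, and power exceeds the target. A statistical analysis plan that is not shown may add an adjusted analysis. Receipt of care is also counted from the service providers, so survey attrition need not remove outcomes; with 250 per arm unadjusted power is about 96.6%. All of this stands, and it limits the point to efficiency. It does not remove it, because the article names the unadjusted test in two sections.

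Three stronger readings are tempting, and the documents do not support them.

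- **That the outcome depends heavily on prior severity.** Referral at the visit depends on the trial's own screen and on mutual agreement. Further referrals in the intervention arm can follow from follow-up answers. The endpoint is receipt of care, not referral, and no strength of association is given.
- **That the precision is free.** The EMR fields are not named, and the Data Sources section lists only self-report and clinic-reported utilisation as primary sources.
- **That covariates could explain 17-38% of the variance.** That range follows if only high-risk participants receive care and 40-60% are high risk: 0.20 × (1 − h)/(h × 0.80) is 0.17 at h = 0.6 and 0.38 at h = 0.4. But it describes risk class measured after the draw, which must not be adjusted for. As an illustration, an EMR diagnosis that predicts receipt only through risk class, with correlation 0.3 to 0.5 to that class, would explain about 1.5% (0.09 × 0.17) to 9% (0.25 × 0.38).

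**Conclusion.** The point holds as a suggestion for a better primary analysis. The planned chi-square is valid and adequately powered under the protocol's own assumptions, but it sets aside pre-randomisation information that may be to hand at little cost. For R² of 2-10%, adjustment at 200 per arm would add about 0.5-2 points of power at 20% versus 35% and about 1-5 points at 20% versus 30%. If the available covariates predict nothing, the gain is nil. The conclusion rests on two things the documents do not settle: that the EMR extract contains a usable substance-use history dated before the visit, and that this history predicts receipt of specialty care to the assumed degree.

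**What to change.** Before unblinding, prespecify as the primary analysis of hypothesis 1 a covariate-adjusted risk difference with 95% CI. Fit a logistic regression of receipt of specialty care on arm, age, sex and EMR-recorded substance-use diagnosis dated before the visit, and standardise the predicted risks over all randomised participants. Include the diagnosis only if the sponsor confirms that the field is available. Keep the chi-square as a supporting test.

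State that DAST-10, AUDIT-C and ASI-Lite as now scheduled are not adjustment variables for this endpoint. Adjusting for them could remove part of the effect or introduce bias.

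The cost is a few lines of text and code, a check of which EMR fields exist, and the need to name the covariates in advance. The sample size need not change. The gain may prove small.
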